### Aims and hypotheses

The primary aim of the current study is to assess the potential of baclofen to prevent relapse in recently detoxified GHB-dependent patients. We hypothesize that administration of baclofen to GHB-dependent patients after detoxification is associated with decreased relapse rates as compared to treatment as usual (without baclofen). We also hypothesize that treatment with baclofen is associated with reduced levels of craving for GHB and reduced psychiatric symptoms levels, including anxiety, and increased quality of life. We expect baclofen treatment to cause minimal side effects in these patients. Finally, we expect a lower drop-out rate from adjuvant therapy (TAU) in the intervention group.

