### Outcome and instruments

#### Primary outcome measures

The primary study outcome is the relapse rate, in other words the level of GHB use as indexed by the total number of abstinent days, the duration of continued abstinence after detoxification (CAD), time before relapse, and intensity of substance use over a period of 3 and 6 months (Timeline Follow-back Method).

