### Statistical analyses

Descriptive analysis will be executed for all measurements and will include the mean, SD and frequencies of events with confidence intervals. Descriptive statistics will be used to compare the basic characteristics of the participants in the experimental group and the control groups. To assess any difference in relapse rates between the experimental group and the control groups (TAU group and matched historical group) at 3 month after detoxification Pearson Chi-squared test will be used for the dichotomous abstinence rates. ANOVA will be carried out on continuous variables, such as the total number of abstinent days, the maximum duration of continued abstinence, time before relapse (relapse defined as ≥ 3 times GHB use per day, for 2 subsequent days), and level of substance use over a period of 3 months. At 6 months period participants who continued baclofen will be compared to those who have stopped with baclofen (after 3 month) on relapse into GHB abuse or abstinence corrected for craving. The numbers of patients maintaining abstinence will be analysed with the intention-to-treat principles. The difference in craving will be analysed by MANCOVA at 3 months between groups (abstinent experimental versus abstinent TAU or relapsed TAU) with DDQ and VAS craving as dependent variables and corrected for craving levels immediately after detoxification. The change in craving in time during the baclofen treatment will be analysed via repeated measures MANOVA. By means of MANCOVA at 6 months after detoxification the difference in craving among participants who are still using baclofen and those who have discontinued baclofen will be analysed corrected for craving after 3 months. The effect of baclofen on the psychiatric symptoms levels (DASS, MINI) and also quality of life (EQ–5D) will be analyzed similarly as for craving at 3 and 6 months. The effects of the different TAU approaches as potential confounders will be tested in a sensitivity analyses (changing one-factor-at-a-time) in an linear regression including TAU per center as covariates.

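### The 3-month comparison of craving, and by extension DASS and EQ-5D, leaves relapsed baclofen patients out, so it does not test baclofen treatment against TAU

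*Protocol article*

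**What the plan says.** The Statistical analyses section of the protocol article sets the 3-month craving comparison "at 3 months between groups (abstinent experimental versus abstinent TAU or relapsed TAU". The two craving scores, DDQ and VAS, are the joint outcomes, and the model adjusts for craving measured at the end of detoxification. Relapsed TAU patients have a place in this comparison; relapsed baclofen patients have none.

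The same section extends the approach to the DASS, the MINI and the EQ-5D: "quality of life (EQ–5D) will be analyzed similarly as for craving at 3 and 6 months".

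Three other statements matter here:

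- Aims and hypotheses puts the secondary hypothesis in terms of treatment, with no restriction to patients who stay abstinent: "treatment with baclofen is associated with reduced levels of craving for GHB and reduced psychiatric symptoms levels".
- Primary outcome measures makes the grouping variable an outcome: "The primary study outcome is the relapse rate, in other words the level of GHB use".
- Intention-to-treat is stated for one analysis: "The numbers of patients maintaining abstinence will be analysed with the intention-to-treat principles".

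No other between-group comparison of these outcomes at 3 months appears. The remaining craving analysis over the treatment period ("The change in craving in time during the baclofen treatment will be analysed via repeated measures MANOVA") concerns the course under baclofen and does not compare it with TAU.

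**The concern.** Relapse is observed after treatment starts, and it is the outcome the drug is meant to change. Forming groups by it selects the successes of one arm and sets them beside the successes or the failures of the other.

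The Background lists craving, anxiety and depression among patients' own reasons for relapse. The document therefore gives cause to expect that relapse status and these secondary outcomes move together. In that case abstinent patients would score better than relapsed patients whatever they were given, and a contrast of abstinent baclofen with relapsed TAU would show that gap as if it came from the drug.

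The craving, symptom and quality-of-life conclusions at 3 months rest on this comparison. Under Implications for practice, a benefit on craving and on psychiatric symptoms is to support larger randomized trials and an interest in patients with high anxiety and depression.

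**Working it through.** **Inputs from the document (Sample size calculation).** Abstinence 70% with baclofen and 36% without; two-sided α = 0.05; 30 per group; 25% dropout; 40 recruited to baclofen.

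**The plan's own figure.** (1.96 + 0.84)² × (0.7 × 0.3 + 0.36 × 0.64) / 0.34² = 7.84 × 0.4404 / 0.1156 = 29.87, so 30 per group; 30 / 0.75 = 40. This reproduces. It concerns the abstinence comparison and is not affected by this point.

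**Patients left out of every group.**

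- At 70% abstinence: 0.30 × 40 = 12 of 40 (0.30 × 30 = 9 of 30).
- If baclofen does nothing, at 36%: 0.64 × 40 = 25.6, about 26 of 40 (0.64 × 30 = 19.2, about 19 of 30).

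The less the drug works, the more of its arm is dropped.

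**Simulation.** 4000 trials per scenario, 30 per arm, baclofen without any effect on craving. The test is the planned one: two craving scores as joint outcomes (Wilks), adjusted for both baseline scores, at 0.05. Assumptions not in the document: correlation 0.6 between the two craving scores; 0.5 between baseline and 3 months; correlation r between liability to relapse and 3-month craving, varied over 0, 0.3, 0.5 and 0.7; no confounding between arms. Negative differences (in SD of the craving score) favour baclofen.

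*No effect on relapse or craving (36% abstinent in both arms): rejection rate, mean adjusted difference*

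| Contrast | r = 0 | r = 0.3 | r = 0.5 | r = 0.7 |
|---|---|---|---|---|
| Abstinent baclofen vs relapsed TAU | 5% | 16%, −0.37 | 44%, −0.64 | 83%, −0.94 |
| Abstinent baclofen vs all TAU | 5% | 10%, −0.23 | 21%, −0.40 | 39%, −0.56 |
| Three groups, omnibus test | 5% | 17% | 50% | 92% |
| Abstinent vs abstinent | 5% | 5%, 0.00 | 5%, 0.00 | 5%, 0.00 |
| All baclofen vs all TAU | 5% | 5%, 0.01 | 5%, 0.00 | 5%, 0.00 |

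Simulation error is small: at 44%, √(0.44 × 0.56 / 4000) = 0.008.

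*Baclofen lowers relapse (70% vs 36% abstinent) but does not act on craving*

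| Contrast | r = 0.3 | r = 0.5 | r = 0.7 |
|---|---|---|---|
| Abstinent baclofen vs relapsed TAU | 12%, −0.24 | 31%, −0.42 | 68%, −0.62 |
| Abstinent baclofen vs all TAU | 7%, −0.11 | 10%, −0.19 | 16%, −0.27 |
| Abstinent vs abstinent | 6%, +0.12 | 9%, +0.21 | 16%, +0.31 |
| All baclofen vs all TAU | 5%, 0.00 | 5%, 0.00 | 5%, 0.00 |

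**Check by hand of the null case.** Under a normal liability with 36% abstinent, the unadjusted gap between relapsed and abstinent patients is r × φ(z) / (p(1 − p)). With z = −0.358 and φ(z) = 0.374, this is r × 0.374 / 0.2304 = 1.62r, or 0.49/0.81/1.14 SD at r = 0.3/0.5/0.7. The adjusted gaps are 0.37/0.64/0.94 SD. The planned correction for post-detoxification craving thus removes roughly a fifth to a quarter of the gap and leaves the rest.

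**The case against.** The strongest points on the other side are these.

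- **These are secondary outcomes in a study that calls itself explorative.** True, and the comparisons of abstinence and GHB use are untouched. But an exploratory label excuses wide uncertainty. It does not excuse a contrast that can favour one arm by construction.
- **The grouping may be of mechanistic interest.** A breakdown by abstinence status can be informative as description. Here it is the only between-group comparison of these outcomes at 3 months.
- **The size is unknown.** This stands. The document does not quantify the craving-relapse link, and with no link there is no inflation. It also does not say whether abstinent or relapsed TAU means two contrasts, three groups or one pooled group, and the error rate depends on which.
- **Handling the other outcomes similarly might mean only baseline-adjusted MANCOVA, without the same groups.** Possible. Taking over the groups is the more direct reading, but the extension to DASS and EQ-5D is less certain than the point on craving, and no separate figures were computed for them.

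A reader might go further in three ways that the document does not support:

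- **That the plan breaks its own intention-to-treat principle.** It promises that principle only for the numbers maintaining abstinence. The accurate statement is that it is not extended to these outcomes.
- **That every contrast here can produce a benefit from nothing.** Abstinent versus abstinent keeps about 5% when baclofen does not change relapse. When baclofen reduces relapse, the bias in this model runs against it.
- **That the same fault applies at 6 months.** There the craving groups are continued versus discontinued baclofen, not abstinence status.

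**Conclusion.** The point holds for the 3-month comparison of craving and, on the direct reading of the text, of DASS and EQ-5D. As written, the analysis omits relapsed baclofen patients and so does not address the hypothesis about baclofen treatment versus TAU. That conclusion follows from the text and needs no simulation.

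The size of the distortion is conditional. With a positive link between relapse and craving and an inert drug, contrasts that include relapsed TAU patients favour baclofen: about 16%/44%/83% false positives against relapsed TAU and 10%/21%/39% against all TAU at r = 0.3/0.5/0.7. Abstinent versus abstinent is unbiased if baclofen leaves relapse unchanged; at the planned 70% versus 36% it is biased against baclofen by about 0.12 to 0.31 SD. These figures rest on the assumed correlations, 30 evaluable patients per arm, and no confounding between arms. The primary outcome and the sample size are not affected.

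**What to change.** At week 12, compare all baclofen patients with all TAU patients regardless of relapse status, for craving (DDQ, VAS), DASS and EQ-5D, adjusted for post-detoxification (T0) values and the covariates already planned. State that relapsed patients in both groups complete the week-12 measures and are analysed in their treatment group. Report any breakdown by abstinence status as descriptive only, without tests of a baclofen effect.

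The cost is a change of wording. Table 2 already schedules VAS, DDQ, DASS and EQ-5D at week 0 and week 12 for both groups, MANCOVA can stay the method, and the sample size does not change.

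The change brings the false-positive rate back to about 5% as far as this selection is concerned. It does not remove confounding: assignment depends on eligibility and patient preference, so the result remains an adjusted, non-randomized comparison and should be reported as such.

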**Table 1 Tab1:** **Baclofen dose in mg/week**

**Week**	**1**	**2**	**3**	**4**	**5**	**6**	**7**	**8**	**9**	**10**	**11**	**12**	**13**	**14**	**15**
Doses a day	15–30	45–60	45/60	45/60	45/60	45/60	45/60	45/60	45/60	45/60	45/60	45/60	30–45	15–30	15–0

Compliance will be assessed based on self-report, urine test for GHB, and empty pill counts. The physician will make use of the BRENDA method, a psychosocial program designed to enhance medication and treatment compliance [33,34]. In case of GHB use during baclofen treatment, participants are expected to contact the research physician. In case of relapse, immediate cessation of treatment will be considered to avoid intoxication hazards.

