### Procedure and data collection

Patients in all treatment conditions (baclofen + TAU or TAU only) will be assessed by research assistants identically in the following time points. Before detoxification, the intensity of GHB abuse (MATE), Quality of life (EQ-5D) and psychiatric comorbidity (DASS) will be assessed. At the end of the detoxification treatment (baseline) and at follow up (three months after start of detoxification) craving (VAS, DDQ), psychiatric comorbidity (MINI plus, DASS), and Quality of life (EQ-5D) will be assessed.

The addiction physician will monitor the participants in the baclofen condition during regular medical check-ups for potential side effects (side effect checklist) and craving (VAS, DDQ), see Table 2. During the follow-up (six months after start of detoxification) the DDQ, DASS, MINI-plus, EQ-5D will be repeated. In summery self-report questionnaires will be administered at the start of detoxification; start of baclofen treatment (week 0), baclofen titration and stabilization (week 1 + 2) and maintenance treatment (week 3–12). Add to that, three months after the end of the baclofen treatment, a follow-up measurements will take place. The research assistant will build up an online Client Record Form from all the questionnaires filled in by the patients. A summary of the medical records will be added by the physician to the electronic patient file.

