**Table 2 Tab2:** **Time measurements**

**Week**	**0**	**1**	**2**	**3**	**4**	**5**	**6**	**7**	**8**	**9**	**10**	**11**	**12**	**13**	**14**	**15**	**24**
Measurement	**T0**-baseline	**T1**											**T2**				**T3**
Mate section	xx												xx				x
EQ–5D	xx												xx				x
DASS	xx												xx				x
Mini-plus	xx												xx				x
Blood	xx						x						x				
Urine	xx						x						xx				x
Medical consult	2x	2x	2x	x	x			x			x		x	x	x		
Baclofen (mg)	0	15–30	45– 60											30–45	30–15	15–0	0
Baclofen Side effect	x	2x	2x	x	x			x			x		x				
VAS	xx	x	x	x	x			x			x		xx				x
DDQ	xx	x	x	x	x			x			x		xx				x
Baclofen withdrawal checklist														x	x	x	
Timeline follow back													xx				x

xx = baclofen group and control group TAU only.

x = baclofen group.

T0 = end of GHB detoxification.

T1 = start baclofen treatment.

T2 = follow-up TAU only and end of baclofen therapy.

T3 = follow-up baclofen group.

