## Discussion

This study protocol presents the design of an open label clinical trial evaluating the efficacy of baclofen to prevent relapse, reduce craving and anxiety, and to assess the safety profile of baclofen in GHB dependent patients. To date, there are no reports on the potential of baclofen to prevent relapse in GHB dependent patients. We expect that baclofen will increase abstinence rates, reduce craving and will be well tolerated. In addition, baclofen may improve psychiatric symptoms such as anxiety and depression, as suggested in several clinical trials in alcohol-dependent individuals [29,30,46].

Several risks of baclofen use are taken into account in the current study. In patients with neuropsychiatric disorders, such as schizophrenia, severe depression, mania, Parkinson’s disease and cerebrovascular diseases, exacerbations of these conditions may occur, when the dose of baclofen is rapidly increased. It may lower the threshold for seizures in epileptic patients [42]. To limit these risks in the current trial, baclofen will be uploaded gradually, over a period of minimally 10 days. Moreover, patients previously diagnosed with any of the mentioned diseases will be excluded from the study.

Abrupt discontinuation of baclofen, when used for several months, can be associated with a withdrawal syndrome which resembles benzodiazepine and alcohol withdrawal. Several symptoms are reported such as hallucinations, fever, confusion, delirium, agitation, insomnia, and muscle stiffness and spasms [47]. Therefore, patients will be advised to taper down slowly when discontinuation is needed.

Intoxication with baclofen has been reported in doses above 100 mg [48]. This risk increases if patients combine baclofen with GHB. Intoxication is not expected when baclofen is administered at a low dose (<30 mg per gift), as applied in the current study. Patients will however, be informed repeatedly of this potential risk and the treatment will be discontinued immediately in case of relapse.

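### Craving during baclofen treatment is to be analysed by a repeated-measures MANOVA that uses complete series only, so the result may describe only the patients who stayed

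*Protocol article*

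**What the plan says.** Method and window (Statistical analyses): "The change in craving in time during the baclofen treatment will be analysed via repeated measures MANOVA". All computations are to be done in SPSS. In the same section intention-to-treat is stated for the abstinence counts: "The numbers of patients maintaining abstinence will be analysed with the intention-to-treat principles".

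Source of the data (Procedure and data collection): "The addiction physician will monitor the participants in the baclofen condition during regular medical check-ups for potential side effects (side effect checklist) and craving". Table 2 places VAS and DDQ at weeks 0, 1, 2, 3, 4, 7, 10 and 12, and again at week 24. Weeks 0 and 12 cover both groups. The others carry the key "x = baclofen group". T2 stands in the week 12 column, and its legend reads "T2 = follow-up TAU only and end of baclofen therapy".

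Relapse and stopping: the text after Table 1 says "In case of relapse, immediate cessation of treatment will be considered to avoid intoxication hazards". The Discussion says "the treatment will be discontinued immediately in case of relapse". These two statements differ and must be reconciled.

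Craving and relapse: the Abstract names craving as one of the main contributors to relapse, and the Background lists it among patients' own reasons for relapsing.

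**The concern.** Repeated-measures MANOVA needs every occasion from every patient it uses. A patient without the week 7 value is removed altogether, including the values at weeks 0 to 4. That matters little if visits are missed at random. Here the protocol's own reasoning links the variable under analysis (craving) to the event (relapse) that may end the window under analysis (baclofen treatment). Patients whose craving rises would then be the more likely to be removed, and those who remain would look better than the arm as a whole.

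The 3-month MANCOVA points the same way: it lists abstinent experimental patients and both abstinent and relapsed TAU patients, but no relapsed baclofen group.

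Reduced craving is a stated hypothesis, and the Implications for practice section makes it part of the case for larger randomised trials. A fall seen only in those who stayed would be a weak basis for that step.

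**Working it through.** **The plan's own figure first.** The sample size section uses (1.96 + 0.84)² × [0.70 × 0.30 + 0.36 × 0.64] / 0.34² = 29.87, so 30 per group. With 25% drop-out, 30 / 0.75 = 40 in the baclofen group. Both reproduce. They concern abstinence; no figure is given for the craving analysis.

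**Occasions.** The VAS and DDQ rows of Table 2 give 8 occasions in weeks 0 to 12, with two measures at each.

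**Expected complete series.** Inputs from the sample size section: 40 patients, 25% drop-out, abstinence 70% with baclofen and 36% without. Assumption: every patient who relapses or drops out loses at least one later visit.

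- Drop-out alone: 40 × 0.75 = 30.
- Abstinence 70%, relapse and drop-out independent: 40 × 0.70 × 0.75 = 21.
- Abstinence 70%, no overlap: 40 × (1 − 0.30 − 0.25) = 18. Full overlap: 40 × 0.70 = 28.
- Abstinence 36%, independent: 40 × 0.36 × 0.75 = 10.8, about 11.
- If, in addition, 5% of values were missing at random at each occasion (assumed), 21 × 0.95⁸ = 13.9, about 14.

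**What the multivariate test needs.** If all 8 occasions enter as separate levels, with VAS and DDQ total, the time effect has 7 × 2 = 14 contrasts and needs at least 15 complete patients. With 21 patients, 21 − 14 = 7 denominator degrees of freedom remain. With 11 this form of the test cannot be computed.

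**Could selection alone produce a fall?** Two simulations were run with the true mean change in VAS set to zero. Every SD, slope and correlation below is assumed; the documents give none.

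- *Relapse driven week by week by VAS* (mean 45, between-patient SD 20, visit SD 10, SD of individual 12-week change 10 to 20, log-odds of weekly relapse 0.03 to 0.05 per VAS point, 25% random drop-out). Complete cases show a false fall of 0.6 to 3.0 points at 70% abstinence and 1.4 to 6.7 points at 36%.
- *Leaving correlated 0.3 to 0.7 with rising craving* (SD of change 10 to 20, 52.5% staying, that is 21 of 40). Completers show a false fall of 2.3 to 10.6 points. With SD of change 15 and error SD 10, a paired test of week 0 against week 12 in 21 of 40 patients finds a significant fall in 13%, 29% and 56% of trials at correlations 0.3, 0.5 and 0.7. The rate is 2.5% when leaving is unrelated to craving.

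**The case against.** The strongest reply is that the documents do not say that craving data stop when baclofen stops. A reader might infer that craving is collected only in patients still on the drug. But Table 2 schedules it by calendar week and by group, not by current use, and the 6-month craving analysis includes patients who have discontinued. A reader might also take the T2 legend to mean that T2 moves forward when a patient stops early. But T2 stands at week 12, and the Procedure section has both conditions assessed identically at three months after the start of detoxification. Both replies stand. What remains is that the article does not expressly say that the week 1 to 10 check-ups continue after stopping. Even if they do, an analysis confined to the treatment period may leave those values out.

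Second, exit at relapse is not certain, given the two conflicting statements, and stopping a drug is not stopping questionnaires. This stands, so the counts are conditional.

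Third, it is tempting to say that the test cannot be run. The article does not fix how the 8 occasions enter the model, and the averaged within-subject form does not need 15 complete patients. It would, however, still use the same complete cases.

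Fourth, the comparison is within patients, so higher baseline craving among leavers does not by itself create a fall; the trajectories must differ. Under the first simulation's SDs, the standard error of a paired change in 21 patients is √(100 + 200)/√21 = 3.8 to √(400 + 200)/√21 = 5.3 points. A false fall of 0.6 to 3.0 points lies below one standard error. This stands too: the larger effects need the stronger assumed correlations.

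Finally, missing-data rules and the scope of intention-to-treat for a secondary outcome may sit in a fuller plan that is not shown. Their absence is not the point here. The point is the method and the window that the article does fix.

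**Conclusion.** The point holds in a limited form. The article fixes a complete-series method for an outcome that it ties to relapse, while relapse may end the period analysed. The result may therefore describe only patients who stayed. On the plan's own rates, about 21 of 40 (18 to 28) would have complete series at 70% abstinence and about 11 at 36%. This assumes that relapsers and drop-outs lose later visits; the figures of 21 and 11 also assume that relapse and drop-out are independent.

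A reader might conclude that any reported fall in craving would be an artefact of survivors. The documents do not support that. The simulated false fall ranges from 0.6 to 10.6 points on a 0 to 100 scale across the assumptions tried at about the planned abstinence rate, and it would vanish if leaving were unrelated to changes in craving. The risk is plausible, and its direction follows whenever rising craving makes leaving more likely, but its size is unknown.

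Severity is modest: this is a within-arm analysis of a secondary outcome in a study that calls itself explorative.

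**What to change.** - Replace the repeated-measures MANOVA with a linear mixed model for VAS and another for DDQ, using all available scheduled occasions from all patients who started baclofen.
- State that the Table 2 craving questionnaires, including T2 at week 12, are kept on the calendar whatever the treatment status.
- Report the on-treatment or completer summary only as secondary.
- Reconcile the two statements on what follows relapse, so that it is clear which patients leave the treatment period.

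The cost is small. Mixed models are available in SPSS, and the questionnaires are already scheduled, so the extra work is following up patients who stop. Some will not return. The mixed model uses what they gave before leaving, but it does not remove bias if leaving depends on craving that was never recorded, which is why keeping the visits matters as much as changing the model. The estimated fall in craving may become smaller. Neither change turns a within-arm fall into an effect attributable to baclofen.

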### Implications for practice

If our study confirms the potential of baclofen to reduce relapse and craving without serious adverse events in GHB-dependent patients, this warrants large scale randomized controlled trials in order to draw more firm conclusions. If baclofen showed to have beneficial effects on psychiatric symptoms in these patients, baclofen might be specific interest for the treatment of those GHB dependent patients with co-morbid high levels of anxiety and depression.

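### The repeated-measures craving analysis has one arm and tests change over time, and no stated analysis compares craving in all baclofen with all TAU-only patients

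*Protocol article*

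**What the plan says.** The craving hypothesis is in Aims and hypotheses: "We also hypothesize that treatment with baclofen is associated with reduced levels of craving for GHB". Implications for practice returns to it: "If our study confirms the potential of baclofen to reduce relapse and craving without serious adverse events".

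Statistical analyses plans three craving analyses:

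- **At 3 months, between groups.** "The difference in craving will be analysed by MANCOVA at 3 months between groups (abstinent experimental versus abstinent TAU or relapsed TAU". The two dependent variables are the DDQ and VAS scores, and the comparison is "corrected for craving levels immediately after detoxification".
- **During treatment.** "The change in craving in time during the baclofen treatment will be analysed via repeated measures MANOVA". No comparator and no group-by-time term is named.
- **At 6 months.** A MANCOVA of patients still on baclofen against those who have stopped it, adjusted for craving at 3 months.

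Table 2 shows who supplies the data. Its legend reads "xx = baclofen group and control group TAU only" and "x = baclofen group". VAS and DDQ carry the double mark at weeks 0 and 12 only. At weeks 1, 2, 3, 4, 7, 10 and 24 they carry the single mark. Procedure and data collection agrees: craving during treatment is followed in the baclofen condition.

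**The concern.** The on-treatment craving series exists in one arm, so the repeated-measures MANOVA can only test whether mean craving is equal at all visits. The hypothesis concerns baclofen against no baclofen. Every patient enters at the end of detoxification and also receives TAU. Craving may therefore move over 12 weeks through recovery, TAU or regression to the mean, and the test can then be significant although the drug does nothing. This holds even with complete data, so it is separate from dropout.

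That would matter little if another stated analysis compared craving between the full groups. None does. A significant time effect in the baclofen arm could then come to stand in for the missing comparison and be reported as support for an anti-craving effect.

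**Working it through.** **1. Which analysis could answer the craving hypothesis?**

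| Analysis | Baclofen patients included | TAU-only patients included | All baclofen vs all TAU? |
|---|---|---|---|
| Repeated-measures MANOVA, during treatment | those on treatment | none | No |
| MANCOVA, 3 months | abstinent only, as listed | abstinent or relapsed, as listed | No |
| MANCOVA, 6 months | continuers and stoppers | none | No |

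In the 3-month MANCOVA the groups depend on abstinence after baseline, which is itself an outcome that baclofen is meant to change. Relapsed baclofen patients are in no listed group.

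**2. Group sizes.** The protocol gives no figure for craving, so the sizes come from its abstinence calculation, which reproduces: (1.96 + 0.84)² × [0.7 × 0.3 + 0.36 × 0.64] / 0.34² = 7.84 × 0.4404 / 0.1156 = 29.87, hence 30 per group; 30 / 0.75 = 40 enrolled on baclofen. I used n = 30 and n = 40 complete patients.

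**3. Rejection rate of the one-arm test with an inert drug.**

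From Table 2: eight occasions (weeks 0, 1, 2, 3, 4, 7, 10, 12) and two measures, giving 7 × 2 = 14 contrasts.

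Assumed, because the documents are silent: craving falls by d SD by week 12 in proportion to f(w) = (1 − e^(−w/4)) / (1 − e^(−3)); DDQ–VAS correlation 0.6; correlation over time ρ = 0.3 to 0.7, either constant across visits or decaying with the gap between them.

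The test is Hotelling's T². It rejects with the probability that a noncentral F with 14 and n − 14 degrees of freedom exceeds its 5% critical value, with noncentrality λ = n m′V⁻¹m (m = mean contrasts, V = their covariance).

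With constant correlation this reduces to λ = n d² × [2 / (1 + 0.6)] × Σ(f − f̄)² / (1 − ρ), where Σ(f − f̄)² = 0.901. For n = 30, d = 0.5, ρ = 0.5: λ = 30 × 0.25 × 1.25 × 0.901 / 0.5 = 16.9. The critical value F(14, 16) is 2.37, and the rejection probability is 45%.

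Range over the assumed correlation structures:

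| Natural fall by week 12 | n = 30 | n = 40 |
|---|---|---|
| 0 | 5% | 5% |
| 0.3 SD | 11–27% | 15–43% |
| 0.5 SD | 24–71% | 40–93% |
| 0.8 SD | 62–99% | 87–100% |

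**4. The same situation with a comparator.** A two-group MANCOVA on week-12 DDQ and VAS, adjusted for week 0, was simulated with 30 against 30 exchangeable patients, an inert drug, ρ = 0.5 and 5,000 runs. It rejected in 5.2%, 5.0% and 4.8% of runs when both arms fell by 0, 0.5 and 0.8 SD. The shared fall cancels.

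**5. Baseline adjustment is not the same as a group-by-time term here.** With a baseline difference between groups, the two estimates differ by (1 − slope) × baseline difference. Assuming a slope of 0.5 and a difference of 0.5 SD, that is 0.5 × 0.5 = 0.25 SD.

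**The case against.** The strongest reply is that the plan never offers this analysis as the test of baclofen. It is described as change over time during treatment, and a one-arm repeated-measures test answers that question. The group comparison is given to the 3-month MANCOVA in the sentence before. The Discussion calls the study explorative and admits the lack of randomisation and placebo, craving is a secondary outcome, and Implications for practice asks for randomised trials before firmer conclusions. Means and confidence intervals are already planned for all measurements.

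Most of this stands, and it rules out several stronger readings that a reader might infer:

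- **That the protocol uses the MANOVA as its efficacy test for craving.** It does not say so. What is open is which analysis carries the craving claim.
- **That recovery will produce a significant result, or that the error rate is far above 5% in any case.** Both depend on a natural fall that the documents do not give. At 0.3 SD the rate may be as low as 11%.
- **That this is the only craving analysis of baclofen patients not limited to abstinent ones.** The 6-month MANCOVA is not limited in that way either.
- **That a two-group comparison would secure a 5% error rate.** That result assumed exchangeable groups. Study design says assignment follows the in- and exclusion criteria and patient preference.

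What the reply does not remove is the gap. The 3-month MANCOVA, on which it relies, is split by post-baseline abstinence and omits relapsed baclofen patients. Calling the study explorative does not change the null hypothesis that a test addresses.

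**Conclusion.** The point holds in a limited form. The repeated-measures MANOVA is a one-arm test of change over time and is not evidence for or against a baclofen effect on craving. No other stated analysis tests the craving hypothesis in all baclofen against all TAU-only patients.

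The gap between the groups actually compared and the hypothesis follows from the text and Table 2 and needs no assumption. The size of the false-positive risk does: it rests on the assumed natural fall, correlations, shape of decline and 30 to 40 patients complete at all eight occasions, although the protocol itself expects 25% dropout. The figures show how the risk grows with the fall; they are not a forecast for this trial. The matter should be corrected, but it concerns a secondary outcome and leaves the abstinence comparison untouched.

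**What to change.** In Statistical analyses:

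1. State that the repeated-measures analysis in the baclofen arm describes the time course of craving, reported as visit means with 95% confidence intervals, and is not evidence of a baclofen effect.
2. Base any statement on baclofen and craving on a 3-month (week-12) MANCOVA of DDQ and VAS that compares all baclofen with all TAU-only patients, whatever their abstinence status, adjusted for week-0 craving.
3. Name this one analysis. Do not offer a group-by-time term as an equivalent, since baseline craving may differ between groups that were not randomised.
4. Say that the nominal 5% error rate holds only if the groups are comparable, and that confounding by eligibility and preference remains.

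The cost is wording. VAS and DDQ are already scheduled in both groups at weeks 0 and 12, so no new data are needed. The downside is that the within-arm p-value can no longer be used to support the anti-craving claim.
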